### **ELIGIBILITY**

Eligibility status must be confirmed by the local investigator or designate and will be confirmed by the provincial PET registry prior to enrollment. It is important that no exceptions be made to the eligibility criteria.

### **Inclusion Criteria**

1. Written informed consent obtained
2. Male, Age  $\geq$  18 years
3. Prior primary treatment for prostate cancer with curative intent such as radical prostatectomy **or** radiotherapy for localized prostate cancer. Unless PET/CT requested as part of Cohort 7.
4. Suspected persistent or recurrent disease defined as one of the following:
  - a. High risk disease at the time of radical prostatectomy characterized by pathologically involved node(s) **or** persistently detectable PSA (>0.1ng/ml) within 3 months post-surgery
  - b. Primary treatment for prostate cancer and biochemical failure (BF) with current management according to the following:
    - i. Following primary radical prostatectomy, BF is defined as rising PSA on at least 2 occasions measured at least 1 month apart and with the most recent PSA measured at >0.1 ng/ml
    - ii. Following primary radiotherapy for localized disease, BF is defined according to the Phoenix Definition, which is rising PSA on at least 2 occasions measured at least 1 month apart and with the most recent PSA measured greater than the nadir PSA + 2.0 ng/ml.

Unless PET/CT requested as part of Cohort 7.
5. Patient scenario falls into one of the 7 pre-defined cohorts. When patient scenario falls outside cohorts 1-6 participation in the Registry must be approved through the established CCO adjudication process for cohort 7.
6. Conventional imaging consisting of bone scan and abdo-pelvic CT scan within 3 months of registration that is either equivocal, negative (no lesions) or positive for oligometastatic disease (4 or fewer unequivocal lesions identified). Registration is defined as Form A: Eligibility is complete.
7. Karnofsky performance status 70 or better (ECOG 0, 1)

### **Exclusion Criteria**

1. Prostate cancer with significant sarcomatoid or spindle cell or neuroendocrine small cell components
2. Extensive metastatic disease on conventional restaging (>4 sites unequivocally positive for disease). Unless PET/CT requested as part of Cohort 7.
3. Prior PSMA PET scan within 6 months of enrollment
4. Patient cannot lie still for at least 60 minutes or comply with imaging
5. Patients falling outside of Cohorts 1-6 where independent adjudication by CCO does not support participation in the Registry

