**Possible PSMA PET/CT informed management**

Observation

Local salvage

Add pelvic node dissection or nodal radiotherapy

Hormone Therapy

Metastasectomy

Stereotactic ablative RT

Hormone Therapy

Chemotherapy

**Cohort 7.** [18F]DCFPyL as a problem-solving tool in patients with prostate cancer when confirmation of site of disease and/or disease extent may impact clinical management over and above the information provided by conventional imaging. All requests for inclusion in the Registry under Cohort 7 will be adjudicated by an expert panel at Cancer Care Ontario. The panel will consist of 3 physicians, including oncologists with prostate cancer expertise and radiologists/ nuclear medicine physicians with PET expertise. The panel will receive a summary of the patient's relevant clinical history, along with supporting documents. The panel will determine whether findings on PET may impact patient management. Decisions will be made by a majority. If the panel cannot reach a decision, input from a second panel of experts may be requested. The final decision of the expert panel will be shared with the study sponsor. In cases where PET is not approved by the panel, referring physician may appeal the decision after providing further clinical information or further explanation on how PET would impact patient management.

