**OBJECTIVES****Primary Objective PREP**

To determine the proportion of men with sites of disease identified at the time of early biochemical failure in high risk disease in men treated with prostatectomy with or without adjuvant or salvage pelvic radiotherapy or hormone therapy as well as men treated with primary radiotherapy. This will be calculated as the number of men with at least 1 PSMA PET detected lesion that is scored as +5 (definitely malignant) or +4 (probably malignant) according to the local imaging read.

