## **STATISTICAL CONSIDERATIONS**

### *Statistical Analyses*

Descriptive statistics will be used to summarize patient, tumour and treatment characteristics, along with endpoints. The primary endpoint will be described using proportions, along with a 95% exact confidence interval, and tested using an exact test of proportions. Secondary endpoints will be summarized using descriptive statistics, along with confidence intervals as appropriate. All tests and confidence intervals will be two-sided and statistical significance will be defined at the  $\alpha=0.05$  level. No statistical adjustments will be performed for multiple testing; however, appropriate caution will be taken when inferring results from this study due to the fact that multiple tests will be

performed. Given the sample size, all tests and confidence intervals will be based on exact or non-parametric methods.

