#### *Sample size calculation*

Conventional imaging can be expected to detect recurrent disease in under 10% of men at the time of biochemical failure. Detection of sites of disease in 30% or more men would be considered a clinically meaningful improvement in performance compared to conventional imaging. For  $H_0=0.10$  and  $H_A=0.30$ ,  $\alpha=0.05$  and  $b=0.10$ , with a two-sided, one-sample test of proportion a minimum sample size of 56 men will be required in each cohort for initial registry analysis. Assuming approximately a 15% dropout a total of at least 65 men per cohort will be necessary or minimum 455 men overall for initial registry analysis. Those cohorts demonstrating positive results will remain open for further access while further regulatory and funding approval is sought.

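### Cohort 7 is exempt from biochemical failure but is still judged by a 10% versus 30% detection test built for men at biochemical failure, so a positive result would not show that PET added anything

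*Protocol*

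**What the plan says.** **The test.** The primary objective is the "proportion of men with sites of disease identified at the time of early biochemical failure in high risk disease", counted as men with at least one lesion scored +4 or +5 on the local read. The Sample size calculation starts from this premise: "Conventional imaging can be expected to detect recurrent disease in under 10% of men at the time of biochemical failure". It then sets the target: "Detection of sites of disease in 30% or more men would be considered a clinically meaningful improvement". It concludes that "a minimum sample size of 56 men will be required in each cohort for initial registry analysis", or 65 with dropout. Under Statistical Analyses, "All tests and confidence intervals will be two-sided", and exact methods are specified. The Null hypothesis section refers to early biochemical failure after prostatectomy. A consequence is attached to the result: "Those cohorts demonstrating positive results will remain open for further access while further regulatory and funding approval is sought".

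**Cohort 7 stays under it.** The Sample Size Revision moves Cohorts 2, 3 and 6 to a precision target. It leaves Cohorts 1, 4, 5 and 7 at 65 men each on the original endpoint. The Phase 2 revision repeats 65.

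**What Cohort 7 is for.** The Cohort 7 paragraph describes a problem-solving use, where knowing the site or extent of disease may affect management beyond what conventional imaging shows. Entry is by adjudication: "The panel will determine whether findings on PET may impact patient management".

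**Who may enter.** Inclusion items 3 (prior curative treatment) and 4 (high-risk disease or biochemical failure) carry a Cohort 7 waiver in both phases. Phase 1 exclusion item 2 also carries one: "Extensive metastatic disease on conventional restaging (>4 sites unequivocally positive for disease). Unless PET/CT requested as part of Cohort 7".

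**The concern.** A one-sample test against a fixed rate means something only if that rate describes the men being tested. The 10% is offered as what conventional imaging finds at biochemical failure. Cohort 7 need not be at biochemical failure and need not have been treated at all, and the protocol gives no conventional-imaging rate for men chosen by a panel as problem cases.

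The endpoint adds a second mismatch. Cohort 7 asks whether PET changes what is done beyond conventional imaging. The endpoint asks whether PET shows at least one suspicious lesion, new or already known. A lesion that was unequivocal before the scan scores as a success. A negative scan that settles an equivocal finding, which may be exactly why the panel approved it, scores as a non-detection.

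At stake is the meaning of a positive Cohort 7 result. It could reflect whom the panel admitted, and it would be read beside the other cohorts while regulatory and funding approval is sought.

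**Working it through.** **1. Does the test cover Cohort 7?** The initial total is 7 × 65 = 455, so all seven cohorts are counted. The revised total is 3 × 425 + 4 × 65 = 1,275 + 260 = 1,535, with Cohort 7 among the four left at 65. It does.

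**2. The plan's own figure.** Inputs from the Sample size calculation: null 0.10, alternative 0.30, two-sided alpha 0.05, power 0.90. With the variance taken at the alternative,

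n = (1.960 + 1.282)² × 0.30 × 0.70 / 0.20² = 55.2, rounded up to 56.

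Dropout: 56 × 1.15 = 64.4, rounded up to 65. Both figures reproduce; the sample size is not in dispute.

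**3. The exact rule at 56 men.** Against 0.10, the two-sided exact p-value is 0.069 at 10 positives and 0.024 at 11. The test rejects at 11 or more, and 11/56 = 19.6%. The chance of reaching 11 is 0.021 at a true rate of 10% and 0.971 at 30%.

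**4. How easily known lesions could carry the test.** Cohort 7's case mix is not given, so this is an illustration. Study Design – Phase 2 Revision reports that 24% of the first 400 registry patients had oligometastatic disease on conventional imaging. Suppose, as an assumption, that the same share of Cohort 7 enters with such lesions, that PET shows each of these men as +4 or +5, and that PET finds nothing in anyone else. The Cohort 7 rate is then 24% with no new lesion found.

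| True rate of +4/+5 in Cohort 7 | Probability of rejecting 10%, n = 56 |
|---|---|
| 0.10 | 0.021 |
| 0.15 | 0.211 |
| 0.20 | 0.58 |
| 0.24 | 0.82 |
| 0.25 | 0.861 |
| 0.30 | 0.971 |

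If PET confirmed only 90% of the men with known lesions, the rate would be 0.9 × 0.24 = 0.216, between the 0.20 and 0.25 rows. With all 65 men evaluable and 2.5% allowed in each tail, the rule is 13 positives (20.0%) and the probability at 24% is about 0.81.

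**5. May men with more than four unequivocal sites enter?**

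| Item | Content | Cohort 7 waiver |
|---|---|---|
| Phase 1 exclusion 2 | Bars more than four unequivocal sites | Yes |
| Phase 1 inclusion 6 | Conventional imaging equivocal, negative, or at most four unequivocal lesions | No |
| Phase 2 exclusions | No extensive-disease item | – |
| Phase 2 inclusion 7 | Same limit of four, only if PSA is above 10 ng/ml | No |

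In Phase 1 the waiver in exclusion 2 has no effect if inclusion 6 is applied as written, and the protocol says that no exceptions are to be made to the criteria. The two items contradict each other. In Phase 2, at PSA of 10 ng/ml or below, no imaging limit applies to any cohort; above 10 ng/ml the limit applies to Cohort 7 as well.

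**The case against.** **Known lesions count in every cohort.** The endpoint is the same throughout, so this part is not peculiar to Cohort 7. That stands. What is peculiar to Cohort 7 is that the null rate does not describe its men and that its stated purpose is gain over conventional imaging.

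**The illustration is chosen against PET.** The same Phase 2 section reports new-lesion detection of 59% in men with negative conventional imaging, across the registry. At a true rate of 59% the test rejects almost surely, and PET would really have added something. This is fair, and it is why 0.82 is not a forecast. But the test rejects in both scenarios and cannot tell them apart, which is the point.

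**The panel guards entry.** Three physicians must judge that PET may affect management. That limits pointless scans, but it does not make 10% the right comparator or change what the endpoint counts.

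**Little hangs on the result.** A positive cohort only stays open, and in any case the Phase 2 revision keeps all cohorts open until each has met its target. Change in management is already a secondary objective for everyone. This reduces the consequence but leaves the stated test and rule in place for Cohort 7.

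**Two stronger readings are tempting.** A reader might infer that Cohort 7 plainly admits men with proven extensive disease. The documents do not settle that, because inclusion 6 points the other way in Phase 1. A reader might also infer that Cohort 7 men pass the test automatically. A cohort passes, not a man. Men without biochemical failure need not have a +4 or +5 lesion, no positivity rate is given for untreated men, and the share entering with known disease is unknown.

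**Conclusion.** The concern holds in this form: for Cohort 7 the 10% null describes a different population, and the endpoint does not measure what the cohort was set up to learn. Rejecting 10% there would not show gain over conventional imaging. This conclusion follows from the text alone and does not depend on the illustration.

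The size is illustrative. Eleven positives of 56 suffice, and if known lesions alone produced a 24% rate, the test would reject about four times in five. That rests on carrying a registry-wide share over to Cohort 7 and on PET confirming all of those men.

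The eligibility contradiction is a separate, firm finding. The problem concerns one cohort of seven and does not touch the sample size arithmetic.

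**What to change.** 1. In the Sample size calculation and both Sample Size Revision sections, take Cohort 7 out of the 10% versus 30% test and out of the rule that keeps positive cohorts open. The target of 65 can stay as an accrual figure.
2. Make change in management (secondary objective 3) its main measure, with an exact 95% confidence interval. With 56 men and a proportion near one half, the approximate half-width is 1.96 × √(0.25/56) = 0.13.
3. Report its +4/+5 rate descriptively, split by whether unequivocal lesions were present on entry imaging, where such imaging was done.
4. Keep Cohort 7 out of any pooled primary detection rate.
5. Reconcile Phase 1 inclusion 6 with exclusion 2 for Cohort 7, and state whether Phase 2 inclusion 7 applies to it. Which way to settle this is for the sponsor and investigators.

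The cost is wording only, since the management questionnaire is already collected. The downside is that Cohort 7 loses a formal hypothesis test.

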## **ELIGIBILITY – PREP PHASE 2**

Eligibility status must be confirmed by the local investigator or designate and will be confirmed by the provincial PET registry prior to enrollment. It is important that no exceptions be made to the eligibility criteria.

### **Inclusion Criteria**

1. Written informed consent obtained
2. Male, Age  $\geq 18$  years
3. Prior primary treatment for prostate cancer with curative intent such as radical prostatectomy **or** radiotherapy for localized prostate cancer. Unless PET/CT requested as part of Cohort 7.
4. Suspected persistent or recurrent disease defined as one of the following:
  - a. High risk disease at the time of radical prostatectomy characterized by pathologically involved node(s) **or** persistently detectable PSA ( $>0.1\text{ng/ml}$ ) within 3 months post-surgery
  - b. Primary treatment for prostate cancer and biochemical failure (BF) with current management according to the following:
    - i. Following primary radical prostatectomy, BF is defined as rising PSA on at least 2 occasions measured at least 1 month apart and with the most recent PSA measured at  $>0.1\text{ ng/ml}$
    - ii. Following primary radiotherapy for localized disease, BF is defined according to the Phoenix Definition, which is rising PSA on at least 2 occasions measured at least 1 month apart and with the most recent PSA measured greater than the nadir PSA +  $2.0\text{ ng/ml}$ .

Unless PET/CT requested as part of Cohort 7.

5. Patient scenario falls into one of the 7 pre-defined cohorts. When patient scenario falls outside cohorts 1-6 participation in the Registry must be approved through the established CCO adjudication process for cohort 7.
6. Karnofsky performance status 70 or better (ECOG 0, 1)
7. If PSA  $>10\text{ ng/ml}$ , conventional imaging consisting of bone scan and abdominal-pelvic CT scan performed within 3 months of registration that is either equivocal, negative (no lesions) or positive for oligometastatic disease (4 or fewer unequivocal lesions identified). Registration is defined as Form A: Eligibility is complete.

### **Exclusion Criteria**

1. Prostate cancer with significant sarcomatoid or spindle cell or neuroendocrine small cell components
2. Prior PSMA PET scan within 6 months of enrollment
3. Patient cannot lie still for at least 60 minutes or comply with imaging
4. Patients falling outside of Cohorts 1-6 where independent adjudication by CCO does not support participation in the Registry

### **Assessment of lesion detection rate**

PSMA PET/CT will be interpreted by local readers. Participating sites will be required to submit a standardized PSMA PET/CT results report. Those patients with four or fewer sites of disease identified on PSMA PET/CT will be classified as “oligometastatic”.

### **Assessment of PSMA PET/CT informed management**

As part of the patient eligibility for PSMA PET/CT referring physicians will complete a PSMA PET Management Impact Worksheet after the PSMA PET/CT information is provided. The questionnaire will ask the physicians to indicate if there was a change in management based on the results of the PSMA PET/CT. Actual interventions following completion of the PSMA PET/CT will be tracked by linkage to provincial registries.

## **STUDY PROCEDURES**

### ***Screening visit***

Urologists and Oncologists will identify potentially eligible patients and will be responsible for obtaining consent and completing pre-PET registration materials. Patient consent forms will be held locally as part of the patient’s medical record.

### ***Patient Approval for PSMA PET/CT***

Registration materials for the requested PSMA PET as part of the registry will be sent to the local PET Centre participating in the registry and reviewed by the local Imaging investigator. Provided all eligibility criteria are met and pre-imaging questionnaires are completed the PSMA PET scan will be scheduled within 6 months of registration. Cancer Care Ontario will also receive registration materials for the purposes of tracking patients on the registry and reimbursement for the PSMA PET/CT scans.

#### *Restaging with [18F]DCFPyL PET/CT (PSMA PET)*

[18F]DCFPyL has a shelf- life of 12 hours and each centre will co-ordinate their process for delivery with the manufacturer, CPDC. [18F]DCFPyL will be administered intravenously at a dose of 325 MBq. The [18F]DCFPyL effective radiation dose equivalent for patients is estimated to be 0.0165 mSv/MBq. This translates to a dose of 5.4 mSv for the injected activity in this study. The CT component is for anatomic correlation and attenuation correction (non-diagnostic) and the radiation dose is 1.5-2.0 mSv. The total radiation dose is estimated to be 6.9-7.4 mSv. For the PET imaging, 60-120 minutes after injection of the [18F]DCFPyL the patient will be asked to void, and then will enter the PSMA PET/CT scanner for acquisition of the PET images with corresponding axial CT images obtained (for anatomic correlation and attenuation correction). Total scan time is approximately 60 minutes.

Following acquisition of the PSMA PET/CT images, interpretation by a local nuclear medicine physician will be conducted. Extent of disease within the prostate and at distant sites will be characterized and delineated on a standardized report. For sites of metastatic disease, suspicious lesions will be identified on PET based uptake characteristics (SUVmax) and correlated with the cross sectional CT imaging and assigned a 5-point suspicion of malignancy scale for each modality separately (+5 definitely malignant, +4 probably malignant, +3 equivocal, +2 probably not malignant, + 1 definitely not malignant). Central readers will be available to provide secondary reads in the case of cases where there is diagnostic uncertainty by the local reader. A report of the PSMA PET/CT will be supplied to the attending physician and a repeat management questionnaire will be completed that identifies any changes in the preferred management strategy based on the results of the [18F]DCFPyL imaging.

#### *Confirmatory Biopsy*

While not mandated by the study, men with restaging studies that suggest disease recurrence are encouraged to undergo biopsy confirmation if local salvage therapies are being considered. For example, those men for whom restaging suggests isolated intra-prostatic recurrence, confirmatory biopsy (either standard TRUS guided biopsy or MRI Guided biopsy) is typically recommended prior to undertaking local salvage therapy. Likewise, those patients with extra-prostatic disease identified on standard or experimental imaging who are being considered for salvage ablative therapies like SBRT for oligometastatic disease are encouraged to undergo confirmatory biopsy prior to salvage.

#### *Follow-up and Outcomes*

Individual sites are required to submit a formalized report from the staging PSMA PET scan to Cancer Care Ontario within 4 weeks of completion of the scan in order to obtain reimbursement for the scan. The report will identify the number and sites of recurrence identified on PSMA PET/CT imaging. Requesting physicians (Urologists and Oncologists) will be asked to complete a PSMA PET/CT management impact questionnaire to determine any change in the preferred management strategies (i.e. change from lesion directed therapy to hormone therapy) based on the information provided by [18F]DCFPyL imaging. Actual management delivered to individual patients after restaging including observation only, biopsy, local or distant salvage or systemic salvage will be assessed at 6 months post imaging through linkage to provincial health registries to track interventions and systemic therapy use.

### **OUTCOMES ASSESSMENT**

#### **Primary Objective PREP**

To determine the proportion of men with sites of disease identified at the time of early biochemical failure in high risk disease in men treated with prostatectomy with or without adjuvant or salvage pelvic radiotherapy or hormone therapy as well as men treated with primary radiotherapy. This will be calculated as the number of men with at least 1 PSMA PET detected lesion that is scored as +5 (definitely malignant) or +4 (probably malignant) according to the local imaging read.

## **Primary Objective PREP Phase 2**

To determine the proportion of men with sites of disease identified at the time of early biochemical failure in high risk disease in men treated with prostatectomy with or without adjuvant or salvage pelvic radiotherapy or hormone therapy as well as men treated with primary radiotherapy when PSMA PET/CT is used without routine prescreening with conventional imaging. This will be calculated as the number of men with at least 1 PSMA PET detected lesion that is scored as +5 (definitely malignant) or +4 (probably malignant) according to the local imaging read.

